## **9.2. Secondary outcomes**

### *Objective functional capacity*

Patients will complete the 6-minute walk test (6MWT) (18) at baseline and 12-week follow-up. Briefly, patients will be encouraged to “walk at their usual pace for six-minutes and cover as much ground as possible” and rest if necessary. The outcomes will be the onset claudication distance (distance walked when the patients related the occurrence of symptom of intermittent claudication (19)) and six-minute total walking distance (6MWD; the maximum distance achieved by the patient at the end of the test). The test will be administered by a trained member of staff and conducted in line with the American Thoracic Society guidance (18). The 6MWT assesses the submaximal level of functional capacity and has good test-retest reliability (19-21), responsiveness (22, 23) and validity (19, 24, 25) in a range of populations including adults with PAD (19).

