#### *Inclusion criteria*

- Diagnosis of PAD confirmed by ankle brachial index  $<0.90$  in one or both limbs
- Age  $\geq 40$  years
- Able to walk distance  $>50\text{m}$
- Live in an area deemed in lowest 30% of super output area from Office of National Statistics

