#### *Exclusion criteria*

- chronic limb threatening ischemia
- short claudication distance  $<50\text{m}$
- severe heart disease (Grade III or IV, New York Heart Association)

- severe ischemic or haemorrhagic stroke or neurodegenerative diseases
- severe hypertension (systolic blood pressure of more than 180 mm Hg, and a diastolic blood pressure of more than 100 mm Hg)
- uncontrolled cardiac arrhythmias (unstable angina during the previous month and myocardial infarction during the previous month)
- a resting heart rate of more than 120 beats per minute
- has already undergone angioplasty, bypass or other surgical intervention for PAD
- other severe comorbid conditions preventing the ability to engage in physical activity, inability or unwillingness to undertake the commitments of the study

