## **11. DATA ANALYSIS**

Primary outcome data will be reported as descriptive statistics, including rates of: patient screening, eligibility, recruitment and retention to 12-week follow-up and survey completion. Qualitative interview data will be analysed thematically to generate themes. Exploratory between-group analyses will be conducted to determine preliminary intervention effectiveness. Normality and homogeneity of variance will be performed using the Shapiro-Wilks and Levene tests, respectively. For comparison of the variables at the pre-intervention, we will perform a one-way ANOVA. To analyze the responses before and after the intervention period, two-way analysis of variance for repeated measures will be used, with the main factors being the group (and the time (pre and post intervention) with Newman-Keuls post-hoc test. The level of significance will be set at  $P < 0.05$ .

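### Onset claudication distance has no value when a six-minute walk is symptom-free, and the planned repeated-measures ANOVA does not suit such a right-censored outcome

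*Protocol*

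**What the plan says.** Protocol section 9.2 (Objective functional capacity) takes two outcomes from one test. The first is "the onset claudication distance (distance walked when the patients related the occurrence of symptom of intermittent claudication (19"). The second is the "six-minute total walking distance (6MWD; the maximum distance achieved by the patient at the end of the test"). On timing: "Patients will complete the 6-minute walk test (6MWT) (18) at baseline and 12-week follow-up". Patients are told to "walk at their usual pace for six-minutes and cover as much ground as possible", and rests are allowed.

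Section 7.1 sets entry by "Diagnosis of PAD confirmed by ankle brachial index" (below 0.90 in at least one limb) and an ability to walk more than 50 m. Claudication itself is not an inclusion criterion. The exclusion list rules out a "short claudication distance" (under 50 m) but sets no upper limit.

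Section 11 gives one method for the pre/post outcomes, with no exception: "To analyze the responses before and after the intervention period, two-way analysis of variance for repeated measures will be used", with group and time as factors. It labels the between-group comparisons exploratory. Section 10 plans 30 patients per arm and says that the findings will inform the power calculations of later definitive trials.

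**The concern.** The first outcome exists only if an event occurs during the test. A patient who walks six minutes at usual pace without claudication has no onset distance. All that is known is that it exceeds the distance walked, so the value is right-censored.

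This can happen at baseline, since entry does not require symptoms, and at 12 weeks, when it is a favourable result. A classical repeated-measures ANOVA uses only patients with both values. If symptom-free tests are entered as blanks, some patients who became symptom-free after randomisation are removed, and more of them come from the intervention arm if the intervention works.

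At stake are the preliminary effect on one of two objective functional outcomes and its standard deviation, both of which could be carried into planning if a later trial uses this outcome.

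**Working it through.** **Figures in the protocol.** For this outcome it gives no mean, standard deviation, effect or symptom-free share, so there is nothing to reproduce. Its only sample-size figure is 30 + 30 = 60. The direction follows from the definitions; the size can only be illustrated.

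**Assumed inputs.**
- Latent onset distance: log-normal, baseline median 120, 160 or 200 m, log-SD 0.5 or 0.7, pre/post correlation 0.7.
- Six-minute walking distance (6MWD): mean 350 m, SD 90 m, correlation 0.4 with baseline log onset distance; it rises by 5 m on control and 30 m on intervention.
- Onset distance: multiplied by 1.05 on control and 1.35 on intervention (a gain of 30 percentage points), or 1.65 (60 points).
- A test is symptom-free when latent onset is at or beyond that patient's 6MWD.
- 400,000 simulated patients per arm.

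**Quantities.** Each is the between-arm difference in mean change.
- Latent: all patients with an onset distance at baseline.
- Complete pairs: patients with an onset distance at both visits.
- Scored: patients with an onset distance at baseline, with a symptom-free 12-week test scored at its 6MWD.
- Share recovered = estimate / latent; attenuation = 1 - share.

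**Results for a 30-point gain.**

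| Median, log-SD | Latent (m) | Complete pairs (m) | Share | Scored at 6MWD (m) | Share |
|---|---|---|---|---|---|
| 120, 0.5 | 40.1 | 35.8 | 89% | 38.1 | 95% |
| 120, 0.7 | 43.0 | 32.3 | 75% | 36.9 | 86% |
| 160, 0.5 | 52.0 | 41.3 | 79% | 45.7 | 88% |
| 160, 0.7 | 53.6 | 35.0 | 65% | 41.5 | 78% |
| 200, 0.5 | 62.5 | 44.7 | 71% | 50.2 | 80% |
| 200, 0.7 | 62.3 | 36.7 | 59% | 44.1 | 71% |

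Complete pairs are attenuated by 11% (1 - 35.8/40.1) to 41% (1 - 36.7/62.3). For a 60-point gain the range is 17% (1 - 66.6/80.5) to 49% (1 - 62.8/123.9). Scoring at 6MWD attenuates by 5% (1 - 38.1/40.1) to 39% (1 - 75.4/123.9) across both gains.

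**Numbers lost.** Across the two gains, symptom-free tests at 12 weeks run from 3% to 24% on control and from 5% to 44% on intervention. Complete pairs fall to between 57 and 36 of 60, before ordinary dropout.

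**Variability.** In a re-run of the same simulation, the control-arm SD of change among patients symptomatic at baseline falls from 58 to 54 m in the mildest scenario and from 124 to 83 m in the heaviest.

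**Direction.**
- No effect on onset or walking distance: complete pairs show no bias beyond simulation noise.
- Harm (onset 20% lower on intervention, 5% higher on control; median 160 m, log-SD 0.6): -34.7 m against -44.0 m, again towards zero.
- Onset unchanged, 6MWD 30 or 60 m further on intervention (median 200 m, log-SD 0.6): complete pairs show a spurious +3.3 or +6.1 m.

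**The case against.** The strongest reply is that the protocol nowhere says symptom-free tests are blank or dropped. Scoring and missing-data rules are commonly left to the SAP, which is not shown, and section 9.2 cites a source for the definition that may carry a convention. This stands against any flat statement that the plan discards its best responders. A reader might infer that, but it is only the default result of a blank under the named method. It does not clear the plan, because the ANOVA is stated and a scoring rule alone leaves part of the attenuation.

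Three further objections hold in part.

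- **Not all lost patients are responders.** Of intervention patients without a 12-week value, 16% to 46% were already symptom-free at baseline in a re-run of the 30-point scenarios, and about 29% to 56% with medians of 120 to 220 m and log-SD 0.7. Losing them narrows the population but is not selection by response.
- **The comparator matters.** A reader might set complete pairs against the latent effect in all patients. With median 200 m and log-SD 0.7 that effect is 76.7 m, and the apparent attenuation is 1 - 36.7/76.7 = 52% instead of 41%. Patients symptom-free at baseline have no measurable change, so that comparison overstates the loss.
- **Much of the gap is the ceiling of the test.** Relative to scoring at 6MWD, omitting pairs costs 6% (1 - 35.8/38.1) to 17% (1 - 36.7/44.1) for a 30-point gain. The rest is distance that a six-minute walk cannot show, and recovering it in metres requires a distributional assumption.

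Finally, this is one exploratory secondary outcome of a feasibility pilot, and section 10 does not say that it will drive the next trial's power. That governs the weight of the point.

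**Conclusion.** The point holds in conditional form and is minor. The protocol pairs an event-dependent, foreseeably right-censored outcome with an ANOVA that needs two observed values. If symptom-free tests are blank and the intervention truly lengthens onset distance, the effect and its variability are probably understated. If they are scored at the distance walked, the understatement is smaller but remains.

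Illustratively, attenuation with blanks is about 10-50% among patients symptomatic at baseline. Every input behind that range is assumed, and the documents cannot narrow it because they give no symptom-free share. A reader might infer a bias towards zero in all cases. That is not supported: there is none without an effect, and a small spurious gain can arise if only walking distance improves. 6MWD has a value for every completed test, so neither it nor the feasibility outcomes are affected.

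**What to change.** - **Section 9.2:** add that a test without claudication is recorded as such, by a tick-box on the case report form, and treated as right-censored at the distance walked. The tick-box should be in place before data collection; otherwise a blank for no symptoms may be indistinguishable from a value not recorded.
- **Section 11:** exempt this exploratory outcome from the ANOVA. Compare arms at 12 weeks with a rank-based comparison that places symptom-free tests highest, or with a baseline-adjusted censored-outcome model (Tobit, or Cox on distance). The rank comparison needs no assumed distribution; the Tobit model gives an effect in metres but relies on one.
- **Reporting:** give the number symptom-free by arm and visit, separately from tests not done.

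The cost is a sentence or two in each section, one tick-box, a little extra analysis, and a less familiar effect measure than a difference in mean metres. 6MWD needs no change on this account.

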### *Subjective functional capacity*

Patients will complete the Walking Impairment Questionnaire (WIQ) (26) at baseline and 12-week follow-up to assess three factors of walking impairment: walking distance, walking speed, and the ability to climb stairs. Patients will be asked how difficult it was to walk in these situations should answer as “none, slight, some, much or unable”. Each domain is anchored from 0, representing extreme limitation, to 100 representing no difficulties. The WIQ has been validated for use in patients with PAD (27, 28).

Patients will also complete the Walking Estimated Limitation Calculated by History (WELCH) questionnaire (29) at both time points. Patients report how long they are able to walk at certain speeds, and then how they would rate their speed of walking relative to their relatives, friends or people at same age. The WELCH has been validated for use in patients with intermittent claudication (30).

### *Quality of life*

Patients will complete the vascular quality of life questionnaire (VascuQoL-6) (31) at baseline and 12-week follow-up. The measure is composed of six items evaluating the impact of vascular disease on social aspects and capacity to perform daily activities. Each item is scored 1-4. The total score is achieved by summarizing the score on each item, resulting in a score between 6 and 24. Higher value indicates better health status. The instrument has good test-retest reliability and validity in patients with PAD (32, 33).

Patients will also complete the EuroQoL questionnaire (EQ-5D-5L) (34) at both study time points which measures five dimensions: mobility, self-care, usual activities, pain/discomfort and anxiety/depression. The digits for the five dimensions can be combined into a 5-digit number that describes the patient's health state (35). The EQ-5D-5L has been widely validated (34, 36) including in patients with cardiovascular disease (37) and as it is used extensively in health research, its inclusion in the current study will enable comparison with previous literature.

### *Dietary quality*

Participants will complete the Short Form Dietary Questionnaire (38) which comprises 24 items that collect data on dietary intake frequency. Participants' responses will be used to derive a dietary quality score. The tool is shown to be a valid method of assessing dietary quality in UK adults (38).

### *Physical activity levels*

Daily ambulatory activity will be assessed using a wrist-worn accelerometer (Fitbit Charge HR) which measures step count, resting heart rate and time in sedentary behaviour as well as light, moderate and vigorous activities. Fitbit devices have been shown to have good concurrent validity for measuring sedentary behaviour and physical activity compared to research-grade accelerometers (39-41). Patients will be instructed to wear the device every day during the study and asked to charge the device every 48-36 hours overnight. Patients' anonymised activity data will be uploaded to the Fitbit online dashboard (Fitabase) and extracted by researchers for analyses.

### *Sleep*

Sleep quality and quantity will also be recorded by the Fitbit device. Patients' anonymised sleep data will be uploaded to Fitabase and extracted by researchers for analyses. Wrist-worn Fitbit devices are shown to have good validity for obtaining gross estimates of sleep parameters (41, 42).

### *Alcohol and tobacco use*

The 3-item Alcohol Use Disorders Identification Test—Consumption (AUDIT-C) screening tool (43) will be administered to patients at baseline and 12-week follow-up to identify alcohol use disorders or risky drinking. The tool has good validity in diverse populations (44, 45). If the patient is suspected to have an alcohol use disorder or risky drinking based on their AUDIT-C score, their general practitioner will be contacted to offer further input and advice.

Patients will complete a standard 30 second carbon monoxide breath test at baseline and follow-up to formally assess smoking status. This is not an aerosol generating procedure and therefore will be appropriate to use.

Self-reported smoking habits will be assessed at baseline and follow-up. Patients will be asked to report their current tobacco smoking status and frequency of smoking cigarettes/other tobacco products and, previous tobacco smoking status.

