### **7.3. Recruitment procedures**

A comprehensive list of patients with PAD attending the Freeman Hospital is already kept. The research team will assess potential suitability and contact the participants by telephone. If the participant expresses interest in the study the PIS and consent form will be forwarded on. Hospital visits will be undertaken for formal consent (baseline) and the follow-up outcome assessments.

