### *Smoking Cessation*

Self-reported smoking habits will be assessed at baseline. Patients who smoke will receive a cessation intervention from the health trainer i.e. discussion of previous quit attempts and benefits of quitting to aid in improving health and exercise capacity. If required, nicotine replacement therapy vouchers which are redeemable at their local pharmacy will be posted to the patient. An eight-week supply of e-cigarette cartridges may also be supplied.

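### The formal measure of smoking status is one carbon monoxide reading per visit, and non-smoker status is not tied to the self-report taken at the same visits

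*Protocol*

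**What the plan says.** Reducing tobacco use is part of a secondary objective (Protocol section 6.4). Section 9.2, under Alcohol and tobacco use, gives two sources of information.

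- The breath test: "Patients will complete a standard 30 second carbon monoxide breath test at baseline and follow-up to formally assess smoking status". No ppm cut-off is given.
- Self-report: "Self-reported smoking habits will be assessed at baseline and follow-up". Its content is: "Patients will be asked to report their current tobacco smoking status and frequency of smoking cigarettes/other tobacco products and, previous tobacco smoking status". No recall period is given, and e-cigarettes and nicotine replacement are not among the items listed.

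Only the breath test is described as formal. Nothing says how the two results are combined, or which prevails if they disagree.

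On timing, section 7.3 says: "Hospital visits will be undertaken for formal consent (baseline) and the follow-up outcome assessments". Patients would therefore ordinarily know the date in advance.

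In section 8, under Smoking Cessation, support is offered on the basis of self-report: "Self-reported smoking habits will be assessed at baseline. Patients who smoke will receive a cessation intervention from the health trainer". The intervention may include nicotine substitutes: "If required, nicotine replacement therapy vouchers which are redeemable at their local pharmacy will be posted to the patient", and "An eight-week supply of e-cigarette cartridges may also be supplied". Section 8.1 describes general recommendations and standard care for the other arm, with no study-supplied substitute.

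Section 10 sets 30 patients per arm. Section 11 calls the between-group analyses exploratory.

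**The concern.** A breath reading at a booked visit shows whether the patient has smoked in the preceding hours. The objective is tobacco use after a 12-week programme. If the reading is taken as the status, a continuing smoker who has gone without for part of a day can be recorded as having stopped. At baseline, the same error would drop a smoker from the group in which abstinence is assessed.

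The self-report could catch this, but as written it is only a parallel item. A question about current status without a time window also leaves a patient who stopped that morning free to answer either way.

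At stake is the meaning of the smoking result and the definition that a definitive trial would inherit. Section 10 says the findings will inform the power calculations of future definitive trials. A later analysis plan can add a cut-off and a combining rule. It cannot recover a 7-day item, or e-cigarette and nicotine replacement use, if these were never asked.

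**Working it through.** The protocol gives no cut-off, smoking prevalence, quit rate or power for smoking, so there is no stated figure to reproduce. The check has four steps. The washout, smoker share, missed shares and quit rate are assumptions, not protocol figures.

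**1. How short an abstinence is enough?** Assume exponential washout, with half-life 2 to 8 h, reading while smoking 15 to 30 ppm and cut-off 6 to 10 ppm.

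Hours to reach the cut-off = half-life × log2(starting reading / cut-off)

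| Start (ppm) | Cut-off (ppm) | Half-life 2 h | 4 h | 6 h | 8 h |
|---|---|---|---|---|---|
| 15 | 10 | 1.2 | 2.3 | 3.5 | 4.7 |
| 15 | 6 | 2.6 | 5.3 | 7.9 | 10.6 |
| 20 | 10 | 2.0 | 4.0 | 6.0 | 8.0 |
| 20 | 6 | 3.5 | 6.9 | 10.4 | 13.9 |
| 30 | 10 | 3.2 | 6.3 | 9.5 | 12.7 |
| 30 | 6 | 4.6 | 9.3 | 13.9 | 18.6 |

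The range is about 1 to 19 h. In much of it an overnight gap or a few hours would do. At the upper end it would not.

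**2. What happens to a continuing smoker under each rule?**

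| Breath reading | Self-report | Reading alone | Both required |
|---|---|---|---|
| Low | Smoking | Non-smoker | Smoker |
| Low | Not smoking | Non-smoker | Non-smoker |
| High | Not smoking | Smoker | Smoker |
| High | Smoking | Smoker | Smoker |

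Requiring both corrects the first row. It does not correct the second, where the patient abstains briefly and also denies smoking.

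**3. What is one patient worth?** With 30 per arm (section 10) and an assumed 30% to 50% smokers, there are 30 × 0.30 = 9 to 30 × 0.50 = 15 smokers per arm. One false non-smoker moves the arm's quit rate by 1/15 = 6.7 to 1/9 = 11.1 percentage points.

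**4. Could the arms differ?** Suppose that nobody truly stops and the reading alone decides. The apparent difference in quit rate is then the share missed under the intervention minus the share missed under usual care.

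- 10% missed in each arm: difference 0.
- 10% missed under usual care and 20% to 30% under the intervention: difference 10 to 20 points. That is 0.9 to 1.8 patients out of 9, or 1.5 to 3 out of 15.

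For comparison, the 95% half-width for a difference in proportions at an assumed 20% quit rate is 1.96 × √(2 × 0.2 × 0.8 / n). This is 37 points for n = 9 and 29 points for n = 15.

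**The case against.** The strongest reply is that the protocol never says a low reading alone makes someone a non-smoker, nor that it overrides a report of smoking. Self-reported current status and frequency are recorded at both visits in both arms, so a smoker who skipped a morning but says so is on record as a smoker. This stands. A reader might infer from the word *formally* that every such patient will be misclassified. The text supports only that this can happen if the formal reading is used alone, or if the self-report is also wrong or ambiguous.

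A reader might also infer a bias in favour of the intervention. The study supplies substitutes only to that arm, and the self-report items listed would not show their use, so the direction is plausible. It is not shown. Vouchers depend on need and cartridges are optional. Eight weeks of cartridges within 12 weeks would run out by the follow-up visit if started in the first 12 − 8 = 4 weeks, and the start is not stated. The protocol does not say what cessation help usual care includes. With equal missed shares the bias is zero.

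Nor do sections 8 and 9.2 contradict each other. One decides who is offered support, the other describes measurement, and using self-report for the first is compatible with both measures for the second.

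Finally, cut-offs and combining rules often belong in a SAP, which is not shown. That is fair for the cut-off and the handling of discordant pairs. It does not dispose of the point, because the protocol itself designates the reading as the formal status and lists self-report items without a time window.

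**Conclusion.** The concern holds in a limited form. The protocol makes a same-day marker the formal measure of smoking status and leaves the self-report beside it, with no recall window and no part in the definition of a non-smoker. If the reading is used alone, a continuing smoker can pass after about 1 to 19 h without smoking, and each such patient shifts the arm's quit rate by about 7 to 11 points.

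The hours rest on the assumed half-life, starting level and cut-off. The points rest on an assumed 30% to 50% smokers, and any binary outcome in 9 to 15 people would show the same shift per patient. They measure sensitivity, not bias. How many patients would be misclassified, and whether more in one arm, cannot be derived from the protocol.

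The point is minor. Feasibility and acceptability are primary, the smoking comparison is exploratory, and half-widths of about 29 to 37 points rule out a firm conclusion on quit rates in any case. It is worth correcting because the change is cheap and some of the missing items cannot be added afterwards.

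**What to change.** In Protocol section 9.2, under Alcohol and tobacco use, and on the matching form:

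- Define a non-smoker, at baseline and at 12 weeks, as a patient who reports no tobacco in the previous 7 days **and** has a breath reading below a stated ppm cut-off. Count any discordant pair as smoking.
- Ask about e-cigarette and nicotine replacement use in both arms. This is descriptive and does not enter the definition.
- Report abstinence at 12 weeks among patients who are smokers at baseline by this same definition.

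The cost is one paragraph of wording and a few extra form questions, with no new procedure. The 12-week abstinence rate will be somewhat lower than with the reading alone. Two limits remain: a patient who abstains briefly and denies smoking still passes, and a 7-day window describes the end of the programme, not the whole 12 weeks.
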